**Fig 2 pone.0313072.g002:**
[figure not shown]
Study methods flow chart.

### Sample/participants

#### Participants

All participants who voluntarily sign up for the GRP will be required to read and sign the informed consent form (See S1 File). The GRP is a project of the Faculty of Nursing and Physiotherapy at the University of Salamanca that offers older people in the city of Salamanca the opportunity to engage in physical exercise. Only those who meet all the selection criteria will be included.

The criteria for participation in the GRP are as follows: being female, over 65 years of age, residing in the community of the city of Salamanca, and meeting the diagnostic criteria for probable sarcopenia according to the EWGSOP2.

Exclusion criteria for participation in the study include previous participation in another exercise program, presence of fibrillations, uncontrolled cardiac pathology or hypertension, pacemaker use, history of severe trauma or recent surgery, congenital collagen involvement, severe mental illness, and any other circumstance that may interfere with the purpose or development of the study, as determined by the investigators. Elimination criteria during the intervention will include total attendance less than 85%, participation in other exercise programs during the intervention period, and changes in physical activity level outside the program.

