Five-Repetition-Sit-To-Stand Test (5STS): this is a functional test that assesses a person’s ability to stand up and sit down from a chair for five times without using the arms (lower extremity strength). The 5STS has been shown to be a more sensitive and specific measure than the original test [33]. It also offers excellent test-retest reliability (0.89) [34].Hand grip test (HG): is a quick, easy and inexpensive test that measures hand grip strength. This test is recognized in clinical practice and in the literature as a standard instrument for measuring HG [15]. It will be performed with the Jamar Plus device in standing position and with the elbow flexed to 90 degrees, which has been shown to have excellent test-retest reproducibility (r>0.80) and excellent inter-observer reliability (r = 0.98) [35, 36].**Secondary functional variables**: the Sarc-f questionnaire will be administered as a rapid diagnostic test for sarcopenia that predicts the need for further evaluation [37]. Physical activity will be monitored through the International Physical Activity Questionnaires (IPAQ) [38]. The Short Physical Performance Battery (SPPB), as it is a rapid, objective three-test physical function test that measures lower extremity strength, gait speed, and balance [39]. The Timed Up&Go (TUG), which is a predictor of frailty and falls, widely used in geriatric research to measure balance and mobility in older people [40]. Gait speed, which is a simple, objective and valid measure of human gait performance that has been used in a variety of settings and is recommended for use as a "vital sign" of health [41]. Two-minute step test to measure aerobic capacity in older adults [42]. The number of falls will also be recorded one year before the start and during the intervention.**Secondary body composition variables**: electrical bioimpedance (TANITA BC-418) will be used to measure most body composition parameters. The total percentage of fat (BF%) and muscle, which is important for general health, will be calculated [43]. Additionally, appendicular muscle mass (ASM) will be calculated, as it is one of the most important variables in the diagnosis of sarcopenia today. It is generally adjusted for height to obtain the appendicular muscle mass index (SMI) (ASM/height^2^). In order to predict the risk of developing chronic diseases, measurements of visceral fat, waist circumference (WC), and body mass index (BMI) (weight/height^2^) will be taken [15]. Height will be measured with a height rod.

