#### Interventions

All study participants will continue with their medical treatment guidelines, level of physical activity, and dietary pattern. Two parallel intervention programs will be designed; the control group will not receive any intervention. The exercise sessions, which will be conducted by healthcare professionals with more than one year’s experience in providing exercise sessions for older adults, will be held at senior centres throughout the city. Adherence to the program will be verified by daily attendance at exercise sessions.

The PT and MT sessions will follow the ACSM recommendations and the basic principles of the FITT-VP (frequency, intensity, type of exercise, time, volume and progression) are followed [44]. There will be three 50-minute sessions per week for 32 weeks. The sessions will begin and end with common exercises, starting with active mobility and ending with stretching and diaphragmatic breathing. The load progression will be based on individual perceived exertion. At the end of each week, participants will be asked to rate their perceived exertion using the modified Borg scale. If the score is less than 7, the intensity of the exercises will be increased for the following week to maintain a consistent level of 7 on the scale. The experienced health personnel delivering the sessions will determine how to progress, such as increasing external weight, repetitions, sets, reducing rest time, or performing unilateral exercises. Although these are group sessions, progression and volume will be adjusted on an individual basis, due to the variability of comorbidities that older adults may present.

The rooms in the senior centres for the interventions will maintain a uniformity in their infrastructure, ensuring in all cases an environment conducive to the optimal realization of the intervention sessions. To encourage adherence, attendance will be collected for each session. If they do not attend, they will be called to their attention, even warning that they may be excluded. Although the number and duration of sessions will be identical in both groups, the nature of the intervention will be different for each study group, and participants will remain unaware of their assignment to a specific group.

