### Data analysis

Statistical analysis will be performed using an intention-to-treat (ITT) approach. Baseline differences between groups will be tested using normality plots and the Kolmogorov-Smirnov test. Homogeneity between groups will be assessed using Levene’s test, thus ensuring successful randomisation. Missing data will be handled using the imputation method of the last observation carried forward. It will be decided to keep outliers in the analysis, as they may represent legitimate outliers or relevant information, which will be discussed in the future study.

A descriptive analysis of the dependent and independent variables of each group will be carried out. Quantitative variables will be expressed as mean ± standard deviation, while qualitative variables will be presented as frequency distributions and percentages.

To assess the effect of the interventions on the study variables in each group, multivariate analysis of variance (MANOVA) will be used as the main method. The variables will be grouped into two large blocks: those measuring functionality (HG, 5STS, GS, TUG, Two-minute step test and SPPB) and those measuring body composition (weight, WC, BF%, visceral fat, ASM, SMI and BMI). Subsequently, MANOVA will be performed on the difference in means after the intervention, using time as an intra-group factor and type of intervention as an inter-group factor. To graphically represent the MANOVA, the canonical Biplot will be displayed, including the confidence circles representing the set of variables in each intervention group. If the circles do not overlap, it can be concluded that there are significant differences between the groups.

To verify the results of the MANOVA, differences between groups for each quantitative variable, both functional and body composition, will be analysed using the repeated measures univariate analysis of variance (ANOVA) test for normal and homogeneous variables or the Kruskal-Wallis test for non-normal or heterogeneous variables. As an additional method, pairwise comparisons will be performed using Bonferroni’s test for normal and homogeneous variables and Dunn’s test for non-normal and heterogeneous variables to determine between which groups there are significant differences.

The effect size in ANOVA of the results obtained in each group will be measured by eta squared (η^2^). Values around 0.01 indicate a small effect size, around 0.06 a medium effect size, and 0.14 or more a large effect size.

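### Intention-to-treat is promised, but women can be eliminated after randomisation on criteria that act differently by arm, and their follow-up and analysis are left unsettled

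*Protocol article*

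**What the plan says.** The Data analysis section sets the principle: "Statistical analysis will be performed using an intention-to-treat (ITT) approach". It adds the missing-data rule: "Missing data will be handled using the imputation method of the last observation carried forward".

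The Participants section, after the inclusion and exclusion criteria, adds a third list: "Elimination criteria during the intervention will include total attendance less than 85%, participation in other exercise programs during the intervention period", and also "changes in physical activity level outside the program". The Interventions section shows that the attendance rule is meant to be used. Absentees are contacted, "even warning that they may be excluded".

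The surrounding design is as follows:
- Outcomes are measured twice, at baseline and at the end of the intervention (Evaluations; Description of the variables).
- Baseline comes before randomisation and the interventions come after it (Evaluations).
- PT and MT each have three sessions a week for 32 weeks. The control group receives no intervention (Interventions).
- The sample size allows 20% loss to follow-up, justified partly by low adherence in older people (Sample size).

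The text shown does not say whether an eliminated woman is invited to the final evaluation, or whether she is analysed in her allocated arm.

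**The concern.** Intention-to-treat keeps every randomised woman in her allocated arm whatever she does afterwards. The elimination criteria act on what she does afterwards. If they decide who is analysed, the comparison is no longer between the groups that randomisation formed.

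The selection also differs by arm. Controls have no sessions to miss, so the attendance rule can remove women only from PT and MT. Women who attend well may differ in prognosis from those who do not, so trimming two arms and not the third can create a difference without any treatment effect. A PT-versus-MT difference in tolerability would also be harder to see, because the women who could not keep up would be gone.

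If elimination instead means only leaving the programme, the women remain in the count. Without a final test, however, their outcome is imputed from baseline. That distorts the comparison in a different way. At stake is the primary comparison on the five-times sit-to-stand test and hand grip. An analysis plan written later cannot recover final tests that were never taken.

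**Working it through.** The plan gives no figure for how many women will be eliminated or what effect this has, so there is none to reproduce. Document inputs are 3 sessions a week, 32 weeks, the 85% cut, and from Sample size the SD of 5 and target difference of 2.5. Everything else below is an assumption.

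**Threshold.** 3 × 32 = 96 sessions. 0.85 × 96 = 81.6, so a woman must attend at least 82. The rule has no meaning for controls.

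**Timing.** Randomisation precedes the interventions and the criteria apply during them, so all three act after randomisation.

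**Reading A: eliminated women leave the analysis.** Suppose there is no true effect, adherence correlates *r* with the outcome change, and the least adherent fraction *q* of an exercise arm is removed. Against a control arm not trimmed on attendance, the spurious difference is

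b = r × SD × φ(z_q) / (1 − q), with SD = 5.

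The factor φ(z_q)/(1 − q) is 0.195, 0.350, 0.497 and 0.644 for q = 10, 20, 30 and 40%.

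| r | q = 10% | q = 20% | q = 30% | q = 40% |
|---|---|---|---|---|
| 0.1 | 0.10 | 0.17 | 0.25 | 0.32 |
| 0.2 | 0.19 | 0.35 | 0.50 | 0.64 |
| 0.3 | 0.29 | 0.52 | 0.75 | 0.97 |

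The range is about 0.1 to 1.0 units, or 0.10/2.5 = 4% to 0.97/2.5 = 39% of the target.

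**Reading B: eliminated women leave the programme and are not tested.** With two assessments, the last observation is the baseline value, so the imputed change is zero. If a fraction *d* of an exercise arm is treated this way, and these women would have had the full 2.5 improvement, the arm's mean change is 2.5 × (1 − d):

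- d = 10%: 2.25
- d = 20%: 2.00
- d = 30%: 1.75

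**How many might be affected.** The documents do not say. With mean attendance of 80 to 90% and a beta-binomial spread between women (precision 8 to 15), about 22 to 63% of an exercise arm falls below 85% of 96 sessions. With mean attendance of 90% and a between-woman SD of 5%, the share is about 16%. The fractions of 10 to 40% used above are therefore plausible but not established.

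**The case against.** The strongest reply is that the article never says eliminated women leave the analysis. The criteria apply during the intervention, and the Interventions section says only that absentees may be excluded. Removal from the programme, with intention-to-treat and carry-forward for those untested, is a coherent reading. This stands. A reader might infer that the two statements cannot both be followed, but the text supports only that it leaves their relation open.

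A reader might also infer that the bias must favour exercise. The documents do not support that, for three reasons:
- Deletion and baseline carry-forward cannot both apply to the same woman, and they can push in opposite directions.
- The activity criterion covers any change, so a control who becomes less active is also eliminable.
- Controls who signed up for an exercise programme may be likelier to exercise elsewhere, but no rate by arm is given and the rule covers all arms.

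Two further inferences go too far. The International Physical Activity Questionnaire is a secondary variable, but no passage names it as the instrument for the activity criterion. Nor can the share of exercise-arm women below the attendance cut be set directly against the 20% loss allowance, which is not split by arm. For example, 24% in two of three equal arms is 24% × 2/3 = 16% of all women, before other losses.

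Finally, the flow chart is not shown, and a condensed article may leave analysis sets to a fuller document. The absence of a per-protocol set is therefore not a fault in itself. That does not answer the point, which rests on two stated rules that need reconciling.

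**Conclusion.** The point holds as an unreconciled conflict between the stated analysis principle and the elimination criteria, and each reading considered here gives a distorted comparison. If eliminated women leave the analysis, it is not intention-to-treat, and PT and MT are trimmed to adherent women while controls are not trimmed on attendance. If they leave only the programme and go untested, they are assigned zero change.

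The sizes are scenarios. The figure of 0.1 to 1.0 units rests on assumed correlations of 0.1 to 0.3 and 10 to 40% removed, and it belongs to the deletion reading alone. The fall from 2.5 to between 2.25 and 1.75 assumes that 10 to 30% are eliminated and would have benefited fully. The net direction is not fixed. Confidence is high in the conflict and in the arm-dependence of the attendance rule, but not in any single size or sign. It should be settled before follow-up ends, because missed final tests cannot be recovered.

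**What to change.** Reconcile the Participants, Interventions and Data analysis sections by stating that:

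1. Meeting an elimination criterion does not remove a woman from follow-up or from the primary analysis.
2. Every randomised woman is invited to the planned final evaluation, whatever her attendance or outside activity, and is analysed in her allocated arm.
3. The criteria define only a per-protocol set, reported as supportive.

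The exclusion warning in Interventions should be worded to match. Whether a woman who meets a criterion stays in the exercise sessions is a separate matter for the investigators, and this change does not touch it.

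The cost is a few sentences, some extra final visits and possibly a smaller estimated effect. No stated figure in the protocol changes.

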#### Sample size

Sample size was calculated for the main study variables, 5STS and HG. The minimum detectable change in similar populations and interventions was 2.5 points (a decrease in 5STS and an increase in HG) to consider a real change beyond measurement error [30, 31]. The study used GRANMO version 7.12 of April 2012. Assuming three groups, with an alpha risk of 0.05 and a beta risk of 0.2 in a bilateral contrast. A loss-to-follow-up rate of 20% was estimated, given that the intervention was extensive and older people are known to have lower adherence to physical activity programs [32]. It was concluded that 105 subjects would be needed among the three groups with a 1:1:1 ratio to detect a difference equal to or greater than 2.5 units, assuming a standard deviation of 5 units.

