**Methods:**

A randomized controlled trial will be conducted with three parallel groups: a PT group, a multicomponent training (MT) group, and a no-exercise group. The inclusion criteria will be women over 65 years of age who meet the diagnostic criteria for probable sarcopenia (Hand grip test less than 16 kg and Five Times Sit to Stand Test more than 15 s) according to the European Working Group on Sarcopenia in Older People (EWGSOP2). Two assessments will be conducted at the beginning and at the end of the 32 weeks of intervention, in which variables of body composition (muscle, fat and weight) and functionality (strength and physical performance) will be collected. There will be 3 sessions of 50 minutes per week in each intervention group. The masking strategy will be double-blind. The analysis of intergroup differences will be conducted using multivariate and univariate analysis of variance (MANOVA and ANOVA), as well as pairwise comparisons (Bonferroni corrections). Changes in the degree of sarcopenia and how many women eliminate the risk of sarcopenia (no probable sarcopenia) after the different interventions will be tested.

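### The printed sample-size inputs do not give 105 as the total over three groups, so the 80% power claimed for a 2.5-unit difference is not supported as written

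*Protocol article*

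**What the plan says.** The Sample size section sets out the calculation in full.

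- Variables: "Sample size was calculated for the main study variables, 5STS and HG". One set of figures serves both.
- Error rates: "Assuming three groups, with an alpha risk of 0.05 and a beta risk of 0.2 in a bilateral contrast".
- Spread: the SD is put at 5.
- Attrition: "A loss-to-follow-up rate of 20% was estimated".
- Result: "105 subjects would be needed among the three groups with a 1:1:1 ratio to detect a difference equal to or greater than 2.5 units".

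The 2.5 units are presented there as the smallest change that exceeds measurement error. The section does not say whether 5 is the SD of a single measurement or of the change. It gives no correlation between baseline and final values, does not name the comparison that was powered, and mentions no multiplicity correction.

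The Data analysis section makes MANOVA on the post-intervention difference the main method, followed by repeated-measures ANOVA, with Bonferroni pairwise comparisons as an additional step. The analysis is by intention to treat, and "Missing data will be handled using the imputation method of the last observation carried forward".

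**The concern.** A difference of 2.5 with an SD of 5 is a standardised difference of 0.5. At 80% power that takes more than 60 evaluable participants per arm in a two-arm comparison. The article's total leaves 35 per arm, or 28 after the assumed loss.

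The section prints every input and a result, so this is not a matter of detail left to a fuller document: the result does not follow from the inputs. At stake is the claim of 80% power for both primary variables. The Discussion's hypothesis depends on power training being better than other exercise and better than no exercise. If the true difference equals the trial's own threshold and the stated SD applies, each pairwise comparison is close to an even chance or worse.

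**Working it through.** **Inputs (Sample size section).** Difference 2.5; SD 5; two-sided alpha 0.05; power 0.80; three equal groups; 20% loss; total 105. Per arm: 105/3 = 35, and 35 × 0.8 = 28 after loss.

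**1. Trying to reproduce 105 as a total**

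*One pairwise comparison.* n per arm = 2(1.960 + 0.842)² × (5/2.5)² = 62.8, so 63 (64 by exact t). Divided by 0.8: 79 (80). Times 3: **237 (240)**.

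*Bonferroni over three pairs, alpha 0.05/3 = 0.0167.* n = 2(2.394 + 0.842)² × 4 = 83.75, so 84 (86 by exact t). Divided by 0.8: 105 (108). Times 3: **315 (324)**.

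*Three-group F test, largest difference 2.5.* The noncentrality is n × Σ(group mean − overall mean)²/25.
- Means 0, 1.25, 2.5: Σ = 3.125, 79 per arm; 79/0.8 rounds up to 99; total **297**.
- Means 0, 0, 2.5: Σ = 4.167, 59 per arm; 59/0.8 rounds up to 74; total **222**.

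*Other readings.*
- One-sided pairwise test: 50 per arm, 63 after loss, 189 in total.
- Paired change within a single group: 40 per group after loss (120 in total) two-sided, or 32 (96 in total) one-sided.
- F test with means 0, 2.5, 5: 21 per arm, 27 after loss, 81 in total.

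None gives 105 as a total. The only exact match is 84/0.8 = 105 **per group**, under the Bonferroni alpha.

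**2. What 105 in total delivers if 5 is the SD of the analysed quantity**

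The noncentrality for two arms of 28 is 0.5 × √(28/2) = 1.871.
- Alpha 0.05: normal approximation Φ(1.871 − 1.960) = 46%; noncentral t **45%**.
- Alpha 0.05/3: Φ(1.871 − 2.394) = 30%; noncentral t **28%**.
- Omnibus F: 36% (means 0, 1.25, 2.5) to 46% (means 0, 0, 2.5).

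With all 35 per arm analysed and the effect undiluted, noncentral t gives 54%, or 36% with Bonferroni.

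Detectable difference at 80% power with 28 per arm: the normal formula gives 2.802 × 5 × √(2/28) = 3.7, and exact t gives **about 3.8**. With Bonferroni, 3.236 × 5 × √(2/28) = 4.3, and exact t gives **about 4.4**.

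**3. What would rescue 105**

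With 28 per arm, 80% power for 2.5 units needs an SD of about 3.3 (2.8 with Bonferroni). If 5 is the SD of a single measurement and change is analysed, the SD of change is 5√(2(1 − r)), where r is the baseline-final correlation. Then r = 1 − 3.27²/50 = 0.79, about 0.8. With Bonferroni, r = 1 − 2.81²/50 = 0.84.

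| r (assumed) | SD of change | Power, 0.05 | Power, 0.05/3 |
|---|---|---|---|
| 0.5 | 5.00 | 45% | 28% |
| 0.7 | 3.87 | 66% | 48% |
| 0.8 | 3.16 | 83% | 69% |

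**The case against.** **The SD may be that of a single measurement.** The planned analysis is of change, and a high correlation would cut the variance. The Description of the variables section cites test-retest reliability of 0.89 for the sit-to-stand test and above 0.80 for hand grip, so a correlation near 0.8 is not far-fetched. This stands as a reason to make the 45% conditional. It does not restore the claim: test-retest values are not correlations across 32 weeks of intervention, and the sample-size section neither states nor uses a correlation.

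**The planned analysis set is 35 per arm, not 28.** Last observation carried forward keeps dropouts in. That is correct, but 54% is then an upper limit. There are only two assessments, so a participant without a final value is given zero change; with 20% such participants the expected difference shrinks towards 0.8 × 2.5 = 2.0.

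**Bonferroni pairs are an additional step and MANOVA is the main method.** This also stands. The 28% belongs to that step and is not the power of the trial as a whole. MANOVA power is not calculated here, because the article gives no correlations among outcomes. But the size is justified by a single difference on each of two variables, not by a multivariate effect.

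**The F test may have assumed means 2.5 apart at each step.** That gives 81, not 105, and it would power a largest difference of 5.

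**Stronger readings that a reader might infer.** One is that the inputs cannot yield 105 at all. They can, as a per-group figure. Another is that the sponsor is shown to have reported a per-group output as a total. The exact match makes this plausible, but the text does not mention a corrected alpha in the calculation, so it remains an inference.

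**Conclusion.** The point holds. As a total over three groups, 105 does not follow from the printed inputs: the between-group tests with a two-sided alpha and a largest difference of 2.5 need 222 to 324, at least twice the stated number.

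The size of the power shortfall rests on 5 being the SD of the quantity analysed. On that assumption, pairwise power is about 45% with 28 completers per arm and at most 54% if all 35 are analysed; with Bonferroni the figures are 28% and 36%. If 5 is instead the SD of a single measurement, 80% pairwise power at 28 per arm requires a correlation of about 0.8 (0.84 with Bonferroni) that the article does not state. A lower correlation leaves the claim unmet.

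These figures treat participants as independent. The Design section describes grouping and assigning participants by senior centre; any effect of that on power is not included.

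**What to change.** 1. Go back to the software output and establish whether 105 was the number per group or the total. Until that is settled, neither the sample size nor the power statement can be relied on. If it was per group, the matching total under these inputs is 315.
2. If 105 in total is kept, replace the 80% claim with what it delivers. For example: with 28 completers per arm and an SD of change of 5, power for a 2.5-unit difference is about 45% pairwise (28% Bonferroni-corrected), and the difference detectable with 80% power is about 3.8 units (4.4 corrected).
3. Alternatively, recompute from a justified SD of the change score, which is what the Data analysis section analyses. State the assumed baseline-final correlation, the comparison powered and the alpha used. Do this separately for the sit-to-stand test (seconds) and hand grip (kg).

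Restating the figure costs one rewritten paragraph and a less favourable stated power, with no added participants. Only a decision to reach 80% power under the stated inputs would require more recruitment.
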